### Screening, Randomization, and Intervention Allocation

Stroke survivors and their primary caregivers were first to be identified by physicians in the abovementioned 5 hospitals. Potential dyads were referred to the 3 NGOs using a standardized referral form developed by the research team. Stroke survivors and their primary caregivers were also identified from the pool of existing service users of the 3 NGOs. The care team consisted of trained social workers from the 3 NGOs who performed screening using a standardized screening form that comprised data on demographics, family functioning, caregiving burden, depressive symptoms, and willingness to join. Participants were recruited if they met the inclusion criteria, passed at least one threshold in the areas of family functioning, caregiving burden, or depressive symptoms, and showed a willingness to join.

After recruitment, trained social workers from the 3 NGOs notified the research team to conduct randomization. To avoid bias and to ensure an equal number in each group within each study site, group allocation was determined using computer-generated block randomization with a block size of 4 by using SPSS Statistics (version 23.0, IBM Corp). A member of the research team informed the care managers about the subject code for group allocation. The participants and researchers were blinded to the group assignment. The care managers and volunteers were not blinded to the group assignment, because they needed to know the participants’ group assignment to provide interventions.

Upon randomization, trained care managers were assigned to different cases by the NGOs’ internal control while 2-3 trained volunteers were assigned to the same group depending on their availability and gender. The research team was cautious about the gender of the volunteers; female caregivers may find it difficult to face many male volunteers due to traditional values, while male caregivers may be more willing to receive support from male volunteers.

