### Protocol Development

The research team developed a standardized protocol consisting of 3 guidelines, that is, a Care Manager Manual (with 4 chapters), an Intervention Group Protocol for Volunteers (with 13 chapters), and a Control Group Protocol for Volunteers (with 6 chapters) to facilitate the intervention program. The research team provided training to the care managers and volunteers separately. First, we conducted a 4-day (32-hour) training session for 9 care managers (3 from each NGO) in 2016, covering the topics of the medical aspects of stroke, the intervention and assessment framework, care management, family therapy, coping with stress, problem-solving, stroke rehabilitation, and family intervention skills. Second, we provided a 5-day (40-hour) training workshop to 46 volunteers recruited by the 3 NGOs, focusing on the impact of stroke, psychoeducation, in-home exercise training, personal care techniques, counseling skills, swallowing and communications, intervention assessment, and code of practice. The number of volunteers recruited was estimated by care managers of the 3 NGOs based on the intervention protocol and resource management.

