**Secondary outcomes**									
	Care Management Strategies Scale	✔		✔		✔			
	Family Caregiver Conflict Scale	✔		✔		✔			
	Cantonese short version of Zarit Burden Interview	✔		✔		✔			
	The Patient Health Questionnaire-9 item	✔		✔		✔			
	Caregiving Ambivalence Scale	✔		✔		✔			
	Social care services used by stroke survivors	✔		✔		✔			
	Medical care services used by stroke survivors	✔		✔		✔			
	Clinical profile and service use data of stroke survivors							✔	
	Cost of study participation							✔	

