#### Secondary Outcome Measures

The secondary outcome is related mainly to the personal level. Personal-level outcome measures include the Cantonese Short Version of Zarit Burden Interview (CZBI-short), Patient Health Questionnaire-9 item (PHQ-9), and Caregiving Ambivalence Scale. The study team will also obtain service utilization records and perform a cost-effectiveness evaluation. The details of each secondary outcome measure are described above (Table 3).

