### Statistical Analysis

We will use descriptive statistics to present baseline characteristics and outcome measures, and we will transform any skewed variables and correct their skewness before inferential analysis. To assess normality, we will perform the Shapiro-Wilk test of normality as well as the normal Q-Q Plot, while we will use the Wilcoxon signed-rank test for the nonparametric test. We will also perform the chi-square or independent two-tailed *t* tests to examine the differences in the baseline characteristics between the intervention and control groups. For the primary and secondary outcomes, we will perform a multi-factor analysis of variance or general linear model to compare the differential changes in each outcome across the 3 assessment time points, that is, T0, T1, and T2 between the 2 treatment groups. This model can account for repeated measures data that are intercorrelated and that produce unbiased estimates even in the presence of the missing data, provided that the data are missing at random. Multivariate regression will be used to compare the differences in the outcomes between the 2 treatment groups and will control for the effect of potential covariates such as depressive symptoms and caregiver burden. Recruitment rate, attrition rate, and missing data will also be examined and reported. All outcome measures will be analyzed based on intention-to-treat principles. Every participant who is randomized according to the randomized treatment assignment will be included. This method of analysis preserves the prognostic balance afforded by randomization [25]. The cost of study participation, including staff cost, travel expenses, and program materials, will be expressed in Hong Kong dollars. All the statistical analyses will be performed using SPSS Statistics. All statistical tests will be two-sided with the level of significance set at .05.

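### Allocation was balanced within study site, but neither planned analysis names site, and the adjusted regression names two trial outcomes as covariates without limiting them to values taken before randomization

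*Protocol article*

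**What the plan says.** **Allocation.** Under Screening, Randomization, and Intervention Allocation, the aim was "to ensure an equal number in each group within each study site", and "group allocation was determined using computer-generated block randomization with a block size of 4". Table 1 lists three sites that differ in kind: an elderly community centre, a post-discharge home support team and a community rehabilitation day centre.

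**Analysis.** The Statistical Analysis section describes two analyses.
- For primary and secondary outcomes, "we will perform a multi-factor analysis of variance or general linear model to compare the differential changes in each outcome" over T0, T1 and T2 between the arms. No covariate and no site term is named.
- A separate multivariate regression comparing the arms, which "will control for the effect of potential covariates such as depressive symptoms and caregiver burden". Site is not named and no measurement time is given.

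**Status of the two covariates.** Under Secondary Outcome Measures, "Personal-level outcome measures include the Cantonese Short Version of Zarit Burden Interview (CZBI-short), Patient Health Questionnaire-9 item (PHQ-9), and Caregiving Ambivalence Scale". Table 3 ticks the burden scale and the PHQ-9 at baseline and at both follow-ups.

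**Timing.** Burden and depressive symptoms are also scored at screening, with the four-item Zarit and the PHQ-2 (Inclusion Criteria). Randomization follows screening and recruitment. T0 is described under Control Group as done by care managers or volunteers before the intervention starts. The randomization section says that these staff are not blinded.

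**The concern.** There are two separate issues.

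**Site.** When allocation is balanced within a factor, the difference between arms no longer carries variation from that factor. A model without the factor still leaves that variation in its residual. Its standard error is then larger than the true one, so the test rejects too rarely and power is lost whenever sites differ in outcome.

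**Covariates.** A covariate measured before randomization cannot be affected by treatment, and adjusting for it is harmless or helpful. A covariate measured at follow-up can lie on the path from treatment to family functioning, or share unmeasured causes with it. Adjusting for it changes the quantity estimated and can bias it. Both named covariates exist in both forms in this trial, and the text does not say which form is meant.

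**Working it through.** The article gives no figure for either issue, so there is nothing of its own to reproduce. The site shares and effects below are assumptions.

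**1. Comparison of outcome level with site omitted**

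Inputs: two-sided α = 0.05 and 80% power (Sample Size Calculation). The nominal signal is therefore 1.96 + 0.84 = 2.80 standard errors. Let R be the share of outcome variance due to site, and k = 1/√(1−R).

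- Balance within site makes the true standard error of the unadjusted difference smaller than the reported one by the factor √(1−R).
- Power without site = Φ((2.80 − 1.96)·k) = Φ(0.84·k).
- Power with site = Φ(2.80·k − 1.96).
- Type I error without site = 2·[1 − Φ(1.96·k)].

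| R (assumed) | k | Power without site | Power with site | Type I error without site |
|---|---|---|---|---|
| 5% | 1.026 | Φ(0.862) = 80.6% | Φ(0.913) = 81.9% | 0.044 |
| 10% | 1.054 | Φ(0.885) = 81.2% | Φ(0.992) = 83.9% | 0.039 |
| 20% | 1.118 | Φ(0.939) = 82.6% | Φ(1.171) = 87.9% | 0.028 |

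A simulation with 200 caregivers, three sites, blocks of 4 within site and a standardized effect of 0.4 agrees. Type I error without site was 0.046, 0.041 and 0.024. Power without and with site was 0.80 and 0.82, 0.82 and 0.85, and 0.84 and 0.88.

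It would be wrong to hold power at 80% without site and credit the whole rise to the site term. Balance in allocation already gives the unadjusted test slightly more than 80%.

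**2. Test of change over time**

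Write the outcome of person i in site s at time t as a site constant, a person term, a group-by-time term and error. In the difference between T1 and T0 the site constant cancels. A stable difference between sites therefore costs the group-by-time test nothing. Only site differences in change matter, and the documents give no basis for sizing those.

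**3. Timing of the covariate**

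Assumed model: an unmeasured trait u (variance 1) raises burden and lowers family functioning, and treatment lowers follow-up burden by 0.5.
- Baseline burden = 0.6u + 0.8e₀.
- Follow-up burden b₁ = 0.6·(baseline burden) + 0.5u − 0.5·treatment + 0.6e₁.
- Outcome = direct effect·treatment − m·b₁ − 0.5u + error.

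Within an arm, b₁ = 0.86u + 0.48e₀ + 0.6e₁, with variance 0.7396 + 0.2304 + 0.36 = 1.33. Adjusting for b₁ leaves the direct effect plus a distortion of −0.5 × 0.5 × 0.86/1.33 = −0.16.

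| Case | True total effect | Adjusted for baseline burden (simulated) | Adjusted for follow-up burden |
|---|---|---|---|
| direct 0.2, m = 0.4 | 0.2 + 0.4 × 0.5 = 0.40 | 0.41 | 0.2 − 0.16 = 0.04 |
| direct 0, m = 0 | 0 | 0.00 | −0.16 |

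The second row shows that the bias need not run toward zero.

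**4. Is T0 before randomization?**

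The article places T0 before the intervention, not before randomization. Three statements suggest that it comes after allocation:
- Randomization follows directly on recruitment.
- Staff who know the allocation carry out T0.
- Only 200 of 264 enrolled caregivers completed baseline questionnaires, so 64 (24%) did not.

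The order is not stated outright. The screening scores are the only ones that the text places before randomization.

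**The case against.** The strongest reply is that this is ambiguity and silence, not error. The term used for the covariates is naturally read as baseline values, and the list is open-ended, so site is unnamed rather than excluded. The article condenses a fuller protocol, and an analysis plan could supply both details. For burden and depression as outcomes, adjusting for follow-up values of the same construct would make little sense, which favours the baseline reading.

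Much of this stands. A reader might infer that the trial will adjust for follow-up mood and burden, or that it chose these covariates in place of site. The documents say neither. The covariates also belong only to the regression, so any such bias would not touch the group-by-time model.

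Two things remain. The article itself states the within-site balance and then describes two analyses that do not use it. And it positively names two covariates that are also outcomes, without a time point. Reading them as T0 values does not settle the matter, since T0 is not placed before randomization.

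A reader might also want a care-manager random effect in the intervention arm, given the "training session for 9 care managers (3 from each NGO) in 2016". The documents do not support that as a finding. Volunteers deliver sessions in both arms and care managers supervise the control volunteers, so nesting in one arm only misdescribes delivery. No intraclass correlation is given, and such terms are commonly left to an analysis plan.

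**Conclusion.** The point holds, at moderate weight.

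- **Site:** the omission makes comparisons of outcome level conservative and does not invalidate them. The loss is about 1, 3 and 5 percentage points of power at assumed site shares of 5%, 10% and 20%. It is nil for the group-by-time test if site differences are stable over time.
- **Covariates:** the wording leaves open an adjustment that could seriously bias the regression estimate. The 0.40 that becomes 0.04 illustrates the mechanism under assumed effects. It does not forecast what this trial will report, because no statement commits the trial to follow-up values.

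**What to change.** In the Statistical Analysis section:

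1. Include study site (the three sites in Table 1) as a fixed effect in every between-arm model, with site by time in the repeated-measures model.
2. State that the depressive-symptom and burden covariates are the screening PHQ-2 and four-item Zarit scores taken before randomization, and that T1 and T2 values are not used for adjustment.
3. State whether T0 came before or after randomization.

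**Cost:** wording only. Site was used in allocation, and the screening form recorded both constructs. Site takes two degrees of freedom per main effect. The short screening scores may explain less variance than the full scales, which is a modest price for covariates that allocation cannot have influenced. Since data collection is complete, the change should be dated and recorded before the arms are compared.

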### Data Handling and Record Keeping

Hardcopies of the data forms will be anonymized after data entry and will be stored in a locked cabinet inside the premises at The University of Hong Kong ([name]). Electronic personal data will be stored in a secured server of the university. The principal investigator will be responsible for safekeeping of personal data during and after the study. The data will be used for academic and clinical research only and will be kept for up to 5 years after the first publication. This study will inform the participants that the institutional review board and ethics committee authority will have access to source data or documents related to this study directly to monitor and review the study.

## Results

The clinical trial began recruiting in January 2017, and recruitment was completed at the end of April 2019. Data collection and data set construction were completed at the end of March 2020. As of March 2020, enrollment has been completed (n=264 stroke caregivers). A total of 200 participants completed the baseline questionnaires. We aim to publish the results by mid-2021. The intervention protocol is in Traditional Chinese only and is available upon request from the corresponding author.

## Discussion

This is the first randomized controlled trial to investigate the effectiveness and cost-effectiveness of a two-tier family-oriented intervention that utilized trained care managers and trained volunteers to support stroke caregivers in Hong Kong. The study results will provide evidence on the feasibility, sustainability, and monetary value, and thus inform stakeholders. Stakeholders include policymakers in various government bureaus and departments such as Labor and Welfare Bureau, Social Welfare Department, and Hospital Authority; health care professionals; social work professionals, including those who provide services in the government, NGOs, as well as the private sector; semiformal caregivers such as foreign domestic helpers; stroke caregivers, stroke patients, and stroke families; and media and social media, on decisions in integrating this new model into the current stroke care services. This intervention attempts to fill a service gap in the current stroke care system and serves as an important basis on which future evidence-based programs supporting family caregivers of stroke survivors could be developed.

This study is not without limitations. First, the latest official statistics that we could retrieve was those of 2016 when this study began. Subsequent statistical data related to stroke patients and caregivers were not available; therefore, statistical data obtained in 2016 formed the basis of our study design. Another limitation is the potential bias and the effect of confounding, but we provided standardized training to all care managers and volunteers to minimize intervention bias.

## Appendix

Multimedia Appendix 1 Demographics of the stroke caregivers and patients with stroke in the randomized controlled trial with 2 groups.

## Abbreviations

CZBI-short: Cantonese short version of Zarit Burden Interview
FAD-GF: Family Assessment Device-General Functioning
FCCS: Family Caregiver Conflict Scale
NGO: nongovernmental organization
PHQ-9: Patient Health Questionnaire-9 item
